## 5. The RE-AIM Framework

The RE-AIM framework provides key indicators for assessing the internal and external validity of the PACO study, which are shown below (see Table 2).

## 6. Data Analysis

Descriptive characteristics of the sample will be reported as means and standard deviations for continuous variables, and frequencies and percentages for categorical variables. Analysis of variance and Chi-square tests will be conducted to determine differences in all variables between study group (i.e., control or intervention) at baseline.

Firstly, the appropriateness of the randomization process will be analysed by exploring outlier values and the normal distribution of the variables using the Kolgomorov–Smirnov test and graphical procedures (normal distribution plots). After inspecting outliers and extreme values, these will be winsorized using the 1st percentile and 99th percentile of the distribution of variables.

Secondly, analysis of covariance (ANCOVA) will be used to analyse the main effects of the study group (fixed factor) on cycling to school, ACS, PA levels, SDT-related variables in ACS, and individual, interpersonal, and environment variables related to ACS from the SEM (dependent variables). The effect size between groups will be calculated according to Lipsey and Wilson (2001), with the following formula: r = [t^2^/(t^2^ + gl)], where t = value of the Student t statistic and gl = degrees of freedom. Additionally, to examine change between baseline and post-intervention, regression models will be used, including the study group in the model as fixed factor and the mean difference (post-intervention minus baseline) of outcome variables as dependent variable.

Finally, to analyse the influence of covariates in the association of the intervention and the main outcome (i.e., cycling to school, ACS, and PA levels), mediation analyses will be performed using the PROCESS macro for SPSS (SPSS Inc., Chicago, IL, USA). For these analyses, the intervention will be included as independent variable and main outcomes as dependent (i.e., cycling to school, ACS and PA levels). Mediators that will be analysed are cycling knowledge, cycling skills, basic psychological needs satisfaction in ACS, motivation for ACS, barriers to ACS from adolescents and parents, and peer social support for ACS.

The following covariables will be included in the regression models: children´s age and gender, date of birth, school grade and name, class, bicycle ownership, parent´s age and gender, weight, height, waist circumference, body mass index, family income, parental educational level, student enrolment, school socioeconomic status, school engagement, population density, city income, distance home-school, cycling lane length, bicycle racks and weather.

Considering that our main aim is to assess real-world effectiveness of the intervention, we will conduct a primary analysis based on an intention-to-treat principle (in which we will analyse participants according to the groups originally assigned). Then, we will conduct a sensitivity analysis per protocol (in which we will exclude participants who did not complete the intervention and/or did not reach a minimum of 75% of attendance).

Analyses will be conducted using the Statistical Package for Social Sciences (SPSS, v. 25.0, IBM SPSS Statistics, IBM Corporation), and the level of significance will be set at *p* < 0.05.

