## 2. Methods

### 2.1. Study Design

The PACO study is a randomized controlled trial setting in public high schools from three Spanish cities (Granada, Jaén, and Valencia), where the schools are the units of randomization, and individuals within the schools are the units of analysis (the participants). The intervention focuses on promoting cycling to school and will be implemented in adolescents during 1 month within the physical education (PE) curriculum classes. Six high schools (i.e., an intervention and a control school in each of the 3 involved cities) will be randomly selected to participate. All study participants will be assessed before and after the intervention period using assessment procedures described below.

The PACO study has been approved by the Review Committee for Research Involving Human Subjects at the University of Granada (Reference: 162/CEIH/2016) and registered with a ClinicalTrials.gov ID: NCT03937336. In addition, the present study protocol has been written in accordance with the Standard Protocol Items: Recommendations for Interventional Trials (SPIRIT) statement (see supplementary file 1).

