### 2.2. Study Population

A total of 360 adolescents aged 14–15 years (3rd grade of secondary education; hereinafter called 3rd grade) from 6 high schools located in 3 Spanish cities will be recruited (see Figure 2). The randomization process is presented in the Figure 2. Within each city, 2 high schools, randomly selected and allocated to intervention or control treatment, will participate in the study. Within each secondary school, two class groups of approximately 30 participants each will be invited to participate and allocated to intervention or control conditions. The final target sample will comprise 360 adolescents (120 adolescents per city; 180 adolescents in the intervention and 180 in the control group).

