#### 4.2.1. Primary Outcomes

(1) Cycling and active commuting to and from school

The Student questionnaire includes the *Mode and Frequency of Commuting To and From School Questionnaire* which has been previously validated with accelerometer in Spanish children and adolescents [60] and its reliability has been recently assessed [61]. It is a 4-item self-report instrument designed to evaluate the usual mode and weekly frequency of mode of commuting in children and adolescents. The four questions included in the questionnaire are: (1) *How do you usually get to school?*; (2) *How do you usually get home from school?*; (3) *How did you get to school each day?*; and (4) *How did you get home from school each day?*; answer options: (a) *walk*; (b) *bicycle*; (c) *car;* (d) *motorcycle*; (e) *bus*; (f) *public bus*; (g) *metro/train/tram*; or (h) *other* (the mode description was required). The final variable to analyse will be the percentage of usual cycling and active modes of commuting to and from school, and the weekly number of cycling and active travels to and from school. Furthermore, two relevant questions closely related to the active commuting behaviour will be completed by the participants: the distance and time to school. The questions are: (1) *How far do you live from school?;* answer options: (a) *<0.5 km;* (b) *0.5 km to <1 km;* (c) *1 km to <2 km;* (d) *2 km to <3 km;* (e) *3 km to <5 km;* and (f) *5 km or more*; and (2) *How long does it take to get to the school since you leave your house?*; answer options: (a) *<15 min;* (b) *15 min to <30 min;* (c) *30 min to <60 min;* and (d) *60 min or more*. Travel time will be classified as “<15 min” if they commuted to school taking less than 15 min and “≥15 min” if they were commuted to school taking 15 min or more [69].

In addition, the parents will complete the family commuting-to-school behaviour questionnaire at home, self-reporting their children´s usual mode of commuting to and from school and the distance and the time to school, using similar questions to those previously reported by the adolescents. A recent study has concluded a very good reliability between children and parents’ self-reports about the mode of commuting to and from school, distance, and time to school in children and adolescents [62].

(2) Physical Activity

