In the search for balance, several pragmatic adaptations will be made to conduct the research in “real-world” scenarios (such as school) where decisions need to be made on how to best conduct the study with the limited amount of time and resources that researchers may have [82]. In the PACO study, these adaptations pertain to the study design, implementation, and evaluation. Firstly, the school teachers will be able to choose the participating class groups, within the same grade. The pilot study and several consultations with school teachers showed that teachers want to choose the participating class and this will increase their involvement in the intervention. Secondly, all high schools in the three participating cities will be included in the random selection processes and then, the chosen schools will be invited to participate. Time limitations do not allow to visit each school for this purpose, and emails to schools have been previously sent (in previous studies of the research group) and they have not been answered because of high workload. Consequently, we will include all the schools in the random process to guarantee that everyone has the same likelihood to be selected. Thirdly, the intervention includes 4 sessions during a 1-month period. Research staff will offer the option to teachers of spreading the 2 h lesson of the 2nd and 4th session in two 1 h sessions using the normal PE schedule. In Spain, the national educational system in secondary schools mandates 2 h per week of PE. Fourthly, regarding the organization of the academic year in 3 trimesters, the study will be implemented in full trimesters to avoid holiday times, including the assessments. Finally, the cycling skills will be assessed by the teacher using a checklist twice during the intervention, simulating real evaluation conditions. However, safety (e.g., to avoid risky activities where children perform skills that they have not learned yet) and time limitations (e.g., lack of more PE sessions to enlarge the intervention), will prevent the cycling skills assessment being carried out at baseline and follow-up, respectively. To summarize, doing research in schools is important to prevent unhealthy behaviours and related beliefs common in our society. Achieving a balance between the scientific requirements of randomized designs and the constraints imposed by real world circumstances is necessary to improve the quality of research conducted in educational settings [83]. It is also consistent with recent calls to achieve a balance between the established evidence-based pathway and a practice-based evidence pathway, and for a more nuanced approach to appraising the utility of diverse types of evidence [84].

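### The outlier and normality check named for judging the randomisation does not use the study group, so its result is unrelated to balance between the arms

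*Protocol article*

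**What the plan says.** Section 6 of the protocol article describes two separate steps before the main models.

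- **Baseline comparison by arm.** "Analysis of variance and Chi-square tests will be conducted to determine differences in all variables between study group", at baseline. This step uses the study group. The text gives it no role in judging the randomisation.
- **Check of the randomisation.** In the next paragraph, "the appropriateness of the randomization process will be analysed by exploring outlier values and the normal distribution of the variables using the Kolgomorov–Smirnov test", together with normal plots. The only action that follows concerns extreme values: "these will be winsorized using the 1st percentile and 99th percentile of the distribution of variables".

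On design, section 2.1 says that "the schools are the units of randomization, and individuals within the schools are the units of analysis". There are six schools, one intervention and one control school in each of three cities. Section 2.2 gives the target as "360 adolescents (120 adolescents per city; 180 adolescents in the intervention and 180 in the control group". Section 7 adds that "the school teachers will be able to choose the participating class groups, within the same grade". Section 6 sets the threshold: "the level of significance will be set at *p* < 0.05".

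Several variables are not continuous measurements. For commuting, section 4.2.1 says "The final variable to analyse will be the percentage of usual cycling and active modes of commuting to and from school". Section 4.2.2 adds a 20-question knowledge score and several scales built from Likert items.

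**The concern.** The question named is whether the randomisation was appropriate. The method named asks whether each variable follows a normal curve and whether it contains extreme values. These are different questions, and the second gives no information on the first.

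This is a stated analysis that does not fit its stated purpose. It is not a detail left to a fuller document.

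What is at stake is the statement on internal validity. Section 7 presents the randomised design as a major strength, so a sentence in the report that the randomisation was found appropriate, or not, would carry weight. The places where comparability could fail are the draw of few schools, the replacement of schools that refuse (section 2.3.1) and the teachers' choice of classes. The named check sees none of them.

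A second, smaller mismatch is that the normality assumption of ANCOVA concerns the residuals of the fitted model, not the raw variables.

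**Working it through.** The plan gives no figure to reproduce here, so the check is one of logic followed by simulation.

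**1. Logic.** Two schools in each of three cities, one per arm, give 2 × 2 × 2 = 8 possible allocations. For a given set of pupils, the pooled values of a baseline variable are the same under all eight. The pooled Kolmogorov–Smirnov (KS) statistic depends only on those values, so its p-value is the same too. As an extreme illustration, a normal sample of 360 was sorted so that all low values fell in one arm. The KS p-value was 0.96, while a two-group t-test gave p of about 4.6 × 10⁻⁸².

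**2. Simulation.** Inputs from the article: 180 v 180 pupils, level 0.05. Assumed: the shapes below, because the article gives no distributions, and an imbalance of 0.5 SD (on the log scale for the lognormal variables; 50% v 60% or 2% v 4% for binary variables). There were 1,000 runs per case. KS is the Lilliefors form, with mean and SD estimated. Entries are the percentage of runs rejecting.

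| Assumed shape | KS, balanced | KS, unbalanced | t-test, balanced | t-test, unbalanced |
|---|---|---|---|---|
| Normal | 4.7 | 3.3 | 5.5 | 99.4 |
| Lognormal, log-SD 0.25 | 93.9 | 94.4 | 4.9 | 100 |
| Lognormal, log-SD 0.5 | 100 | 100 | 4.5 | 99.1 |
| Lognormal, log-SD 0.8 | 100 | 100 | 3.7 | 98.5 |
| Mean of four 1–5 items | 100 | 100 | 5.4 | 99.7 |
| 20-item score | 100 | 100 | 5.8 | 99.7 |
| Binary, 50% | 100 | 100 | 5.1 | 48.4 |
| Binary, 2% | 100 | 100 | 4.3 | 19.7 |

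The two KS columns are nearly the same in every row. The t-test columns differ because that test uses the arm.

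**3. Sensitivity.**
- Normal variable, shifts of 0.3, 0.5, 0.8 and 1.0 SD: KS rejects in 4.0%, 3.5%, 3.8% and 5.3% of runs, the t-test in 82% to 100%.
- 90 v 90 pupils (the 50% loss allowed for in section 2.3.3): KS rejects in 3.8% (balanced) and 4.4% (unbalanced) for the normal variable, 64% and 70% for the mildest skew, and 98.5% to 100% for the rest.
- The article does not say which form of KS is meant. Without the Lilliefors correction, at 180 v 180, rejection with balanced and unbalanced arms is 0% and 0.1% (normal), 37% and 40% (mildest skew), 92% and 94% (item mean), 96% and 91% (20-item score), and 99.9% to 100% for the others. The level changes; the lack of any useful relation to balance does not.

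**4. The planned baseline tests by arm.** These use the study group but treat pupils as independent. With 60 pupils per school and intraclass correlation ICC, the variance of an arm mean is inflated by 1 + 59 × ICC. A nominal 5% two-sided test then rejects with probability 2 × [1 − Φ(1.96 / √(1 + 59 × ICC))] under a sound allocation. The ICC values are assumed, and city effects are ignored.

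| ICC | Inflation | By formula | Simulated (4,000 runs) |
|---|---|---|---|
| 0.01 | 1.59 | 12.0% | 12.0% |
| 0.05 | 3.95 | 32.4% | 33.1% |
| 0.10 | 6.90 | 45.6% | 45.5% |

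So these tests can reveal an imbalance, but a small pupil-level p-value is not evidence that the randomisation failed.

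**The case against.** The strongest reply is that this is a wrong opening clause on an ordinary screening step. Section 6 attaches no decision to the KS result. The only action is winsorising, and no estimate, analysis set or conclusion depends on the test. That stands, and it is why the point is minor. The clause still needs correcting, because it states a purpose that the method cannot serve.

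The second reply is that the plan as a whole would show an imbalance, since the preceding sentence compares all variables by arm. That also stands. What it leaves open is that the text does not connect those tests to the randomisation, and that they ignore the school as the unit allocated.

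A reader might infer something stronger: that the plan would declare a sound randomisation faulty almost every time and let an unbalanced one through. The documents do not support this, for four reasons.

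- The two halves do not hold for the same variable. Non-normal variables tend to be flagged whether or not the arms are balanced; normal ones are rarely flagged either way.
- No rule turns a KS rejection into a verdict on allocation.
- The baseline tests by arm mean that an imbalance would not simply pass unseen.
- Section 6 opens by separating continuous from categorical variables, so it is not clear that the KS test would be run on the yes/no commuting variables. For the others, the rate of flagging rests on assumed shapes.

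**Conclusion.** The concern holds in a limited form. The check named for the randomisation does not involve allocation, so it cannot support a statement in either direction. That conclusion follows from the definition of the test and needs no assumption about distributions. The rejection rates do rest on assumed shapes: about 5% for a normal variable with the Lilliefors form, balanced or not, and 94% to 100% at 360 pupils for the clearly non-normal shapes tried.

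Severity is minor. The sentence does not by itself bias the treatment estimate; the harm is confined to what the report could claim about the randomisation.

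**What to change.** In section 6:

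1. Describe the outlier and normality step as data screening only, and check normality on the residuals of the fitted models rather than on raw variables.
2. Base any statement on the randomisation on the allocation record: the order of the school list, the arm drawn in each city, refusals and replacements, and how classes were chosen.
3. Add a descriptive baseline table by arm and by school within city. Do not read the pupil-level baseline p-values as a test of the randomisation.
4. State that each outcome with a baseline measurement is adjusted for its own baseline value in the ANCOVA. These values are already collected, but the covariate list in section 6 does not name them. Cycling skills are not measured at baseline (section 7) and fall outside this.

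The cost is a few sentences and a wider baseline table, with no new data, staff or pupils. One small downside is that, with three schools per arm, baseline differences will often look large by chance and must be reported as such.

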## 1. Introduction

### 1.1. Active Commuting to School: Benefits, Prevalence and School-Based Interventions

The physical, psychological, and social benefits of meeting physical activity (PA) recommendations (i.e., 60 min of daily moderate-to-vigorous PA [MVPA]) have been well-documented in the scientific literature [1]. However, four out of five adolescents do not meet these MVPA guidelines [2]. Specifically, in Spain, 76.6% of adolescents between 11 to 17 years old are insufficiently active [2]. Since previous studies have shown that PA patterns in childhood track to adulthood [3], promoting regular PA levels in young people is a public health concern [4].

Active commuting to and from school (ACS) is defined as any walking or cycling to and from school; while passive commuting refers to the use of motorized vehicles as a mode of commuting, such as by car, bus, metro, train, or motorcycle, among others [5]. ACS in adolescents is a routine behaviour that is associated with higher levels of PA on schooldays [6,7,8], less time spent in sedentary pursuits [9] and has social and mental benefits [10]. Compared to walking, cycling to school leads to significantly higher physiological benefits, particularly regarding cardiorespiratory fitness, due to its higher PA intensity [6]. In addition, ACS also has environment and economic benefits [11]. Moreover, getting young people physically active during their trip between home and school is currently one of the main priorities of global policies, such as the Global Action Plan on Physical Activity 2018–2030, promoted by the World Health Organization [12], and the 2030 Agenda for Sustainable Development, promoted by the United Nations [13].

However, despite the well-known benefits associated with ACS, fewer than half of adolescents globally use ACS [14], with large variability across countries [9]. In Spain, about 50% of adolescents reported walking to school and only 0.3% reported cycling to school [15]. Although 68.2% of Spanish adolescents and young people aged 12 to 24 years already own a bicycle and 92.2% of them could ride a bicycle [16], less than 2% reported cycling to school [15,17,18,19]. Given that cycling to school tends to track from childhood to adolescence [20], along with its documented benefits, promoting this health-related behaviour should be a public health priority.

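### Winsorising at the 1st and 99th percentiles does not exempt the commuting outcomes, so it can cap or erase genuine cycling trips; separately, ANCOVA p-values for rare cycling are unreliable

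*Protocol article*

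**What the plan says.** Section 6 (Data Analysis) of the protocol article begins with a screening step, described as "exploring outlier values and the normal distribution of the variables". After that inspection, outliers and extreme values are to be altered: "these will be winsorized using the 1st percentile and 99th percentile of the distribution of variables". No variable is named and none is excluded.

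The same section then states that "analysis of covariance (ANCOVA) will be used to analyse the main effects of the study group (fixed factor) on cycling to school", on active commuting to school (ACS), on physical activity and on the other study variables. A further regression takes "the mean difference (post-intervention minus baseline) of outcome variables as dependent variable". No binary or count model is named for the commuting outcomes.

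Section 4.2.1 defines those outcomes in two forms. One is usual mode: "The final variable to analyse will be the percentage of usual cycling and active modes of commuting to and from school". This is a yes/no item for each pupil. The other is the number of cycling and active trips in the week.

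Section 1.1 gives the expected level of cycling among Spanish adolescents: in one place "only 0.3% reported cycling to school", in another "less than 2% reported cycling to school". It puts walking at about 50%. Section 2.2 sets the sample at 360 pupils, 180 per arm.

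**The concern.** Percentile winsorising assumes that values in the extreme tail are noise or error. For a variable that is zero for almost everyone, the upper tail is made up of the pupils who show the behaviour. If fewer than about 1% of pupils cycle, the 99th percentile is zero, and the rule turns cyclists into non-cyclists. If slightly more cycle, it pulls the frequent cyclists down to the level of the occasional ones.

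Cycling to school is a primary outcome and the behaviour that the intervention targets. If new cyclists appear mainly in the intervention arm, capping their trips shrinks the estimated effect. The change-score analysis is also exposed, because the cited background rates apply most directly at baseline, where cyclists are fewest.

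A second, separate issue is the linear model. With only a handful of cyclists, the t-based p-value rests on an approximation that does not hold.

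**Working it through.** **Inputs.** N = 360, with 180 per arm (section 2.2). Cycling prevalence is 0.3% to under 2% (section 1.1). The cut points are the 1st and 99th percentiles (section 6). Assumptions: percentiles are taken on the pooled sample; a pupil can make at most 10 trips a week (two a day on five school days); all 360 pupils provide data. The article does not give a percentile definition. SPSS is the named software, so its weighted-average definition is used first and other common definitions second.

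**Step 1: expected cyclists.** 360 × 0.003 = 1.08 and 360 × 0.02 = 7.2 in total, or 0.54 to 3.6 per arm.

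**Step 2: where the 99th percentile falls.** Under the weighted-average definition its rank is 0.99 × (360 + 1) = 357.39. The cap is therefore the 357th ordered value plus 0.39 times the gap to the 358th. With k cyclists, the non-zero values occupy the top k ranks.

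| Cyclists, each with 10 trips | Cap, weighted average | Total before → after | Other definitions tried |
|---|---|---|---|
| 1 or 2 | 0 | 10 or 20 → 0 | 0 |
| 3 | 0.39 × 10 = 3.9 | 30 → 11.7 | 0 |
| 4 | 10 | 40 → 40 | 0, 16.4 or 40, by definition |
| 5 or more | 10 | unchanged | unchanged |

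The yes/no item follows the same thresholds if the rule is applied to it. It is erased with 1 or 2 cyclists, depends on the definition with 3 or 4 (0.83% and 1.11%), and is unchanged from 5 upwards (1.39%). With N = 300 the pattern is similar: 1 or 2 erased, 3 borderline, 4 or more unchanged.

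**Step 3: how likely full erasure is.** Erasure needs at least one cyclist, so the relevant quantity is P(k = 1) + P(k = 2) for a Binomial(360, p), with the same rate in both arms:
- p = 0.3%: 0.367 + 0.198 = 0.57
- p = 1%: 0.098 + 0.177 = 0.27
- p = 2%: 0.005 + 0.019 = 0.024

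**Step 4: trip counts with more cyclists.** The trip patterns here are illustrative.
- Five cyclists with 2, 2, 4, 6 and 10 trips: the 357th and 358th values are 2 and 4, so the cap is 2 + 0.39 × 2 = 2.78. The total falls from 24 to 2 + 2 + 3 × 2.78 = 12.3 (10 under the other definitions).
- Six cyclists with 1, 2, 2, 4, 8 and 10 trips: the cap is again 2.78. The total falls from 27 to 1 + 2 + 2 + 3 × 2.78 = 13.3 (11 under the others).

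About half of the recorded cycling is removed in each case, at counts where the yes/no item is untouched.

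**Step 5: linear-model p-values for rare cycling.** Unadjusted comparison, 180 per arm, clustering ignored:

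| Cyclists, control vs intervention | Linear-model p | Fisher exact p |
|---|---|---|
| 0 vs 4 | 0.044 | 0.123 |
| 0 vs 5 | 0.024 | 0.061 |
| 1 vs 7 | 0.032 | 0.067 |

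Over repeated samples at a nominal 5%, the simulated type I error of the linear test is 0.3% at a rate of 0.3%, 3.7% at 1% and 4.5% at 2%. On average the test is conservative, yet it can cross 0.05 at particular small counts where exact inference does not.

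**The case against.** **The rule may not reach the yes/no item.** It acts on outliers found on inspection, within a step about normality, and section 6 separates continuous from categorical variables when it describes the sample. That stands: recoding a yes/no answer is a possible reading, not a stated intention. It does not protect the weekly trip count, which is numeric and mostly zeros.

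**The signal is not deleted in general.** A reader might infer that winsorising removes the cycling effect. An effect large enough to detect would move the count past the threshold: at 0.3% against 2%, the chance of 2 or fewer cyclists is 22%. For the yes/no item, winsorising changed no verdict at p < 0.05 in simulation, and power was the same with and without it (31% at 0.3% against 2%). Counts small enough to be erased, such as 0 against 3 (p = 0.08), were not significant anyway. This stands for the yes/no item. The distortion of trip totals and of the estimates remains.

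**ANCOVA is not wrong for every commuting outcome.** A reader might extend the criticism to ACS. With about 50% walking, ACS is common and the simulated type I error is about 5%. Nor is the linear difference in proportions biased by a yes/no outcome in a randomised comparison. The problem is confined to p-values and standard errors for rare cycling.

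**The odds ratio does not help the argument.** Section 2.3.3 attaches its odds ratio of 1.5 to physical activity, so it cannot show that the commuting analysis departs from its own sample-size metric.

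**The obvious alternatives have limits.** A plain binomial model for trips out of 10 treats one pupil's trips as independent. If cyclists make all 10 trips, its type I error is about 55% at 2% in both arms. School-level randomisation inference with three pairs has 2³ = 8 allocations, so its smallest two-sided p is 2/8 = 0.25. Both points stand and shape the fix.

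**Conclusion.** The point holds in a limited form. As written, the winsorising rule can alter genuine values of a primary outcome at the cycling rates that the article itself cites. Full erasure of cycling trips needs 1 or 2 cyclists among 360 under the weighted-average definition, with probability 57%, 27% and 2.4% at 0.3%, 1% and 2%. Partial loss of trip counts, by about half in the illustrations, extends to five or six cyclists. The yes/no item is at risk only near or below 1% prevalence and only if the rule is applied to it.

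Separately, the p-value from the named linear model is unreliable for cycling at these counts. Neither conclusion extends to ACS or to the estimated difference in proportions.

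The results rest on pooled percentiles, on the assumed trip patterns, on background rates that may not hold after the intervention, and on calculations that ignore clustering by school. The plan should be corrected before analysis, because the cleaning step changes primary outcome values.

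**What to change.** In section 6:

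- Exempt the cycling and ACS outcomes, both usual mode and weekly trips, from winsorising. Limit outlier handling to implausible values of continuous measures, and keep the unaltered data as the primary analysis.
- For cycling, report counts and the risk difference by arm and by school. Replace the ANCOVA p-value with a small-count method such as an exact test. State that a pupil-level exact test ignores allocation by school, and that school-level randomisation inference with three pairs cannot give a two-sided p below 0.25.
- If weekly trips are modelled as a proportion of 10, allow for overdispersion within pupil and do not use a plain binomial model.

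The cost is a change of analysis wording and procedure, with no further data collection. The real downside is weaker formal inference for cycling, which should be stated openly.

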#### 2.3.3. Sample Size Calculations

A minimum sample size of 300 participants will be needed to detect an odds ratio of 1.5 in the primary outcome (i.e., PA), assuming an alpha error of 0.05 and 80% of statistical power [51]. Therefore, 50 participants regardless of gender per school (6 schools) are needed. To account for the potential loss to follow-up of up to 50% participants regardless of gender (based on investigators’ previous experience due to the use of wearable devices), a total of 360 adolescents will be recruited (i.e., 120 participants per city). The groups randomization will be done at a 1:1 ratio at city level (i.e., from each city, 60 participants will be randomized to intervention and 60 to control groups).

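### The effect size labelled r is printed without a square root, so as written it is r² (partial eta squared from the ANCOVA), not r

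*Protocol article*

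**What the plan says.** Section 6 states that "analysis of covariance (ANCOVA) will be used to analyse the main effects of the study group (fixed factor"). The dependent variables are cycling to school, active commuting, physical activity, the self-determination variables and the other social-ecological variables. The next sentence attributes the between-group effect size to a cited methodological source and gives it "with the following formula: r = [t^2^/(t^2^ + gl)], where t = value of the Student t statistic and gl = degrees of freedom".

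No radical sign or exponent of one half appears in that formula. Nowhere else does the article restate it, call the quantity r² or eta squared, give cut-offs for reading it, or state an expected t or r. It is the only effect-size measure that section 6 names. Because it follows directly on the ANCOVA, it reaches all three primary outcomes listed in section 4.2.

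**The concern.** The label and the expression disagree. The letter r denotes a correlation, while t²/(t² + df) is the square of one. An analyst who follows the plan literally would report a squared quantity under the name of the unsquared one.

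At stake is how the results are read. Squaring a number below 1 shrinks it, and shrinks small values proportionately most. Small effects are plausible here: section 1.1 reports that earlier reviews of school-based commuting interventions found non-significant results or small effects. A modest effect, printed as r and read or pooled as a correlation, could pass for almost none.

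**Working it through.** **The identity.** For two groups, the t statistic and the group–outcome correlation satisfy t² = r² × df/(1 − r²). Solving for r² gives r² = t²/(t² + df), hence |r| = sqrt[t²/(t² + df)]. In an ANCOVA the two-level group factor has one degree of freedom, so F = t². Partial eta squared is F/(F + error df) = t²/(t² + df), the same expression.

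**Numerical confirmation.** One simulated data set with 150 per group gave t = 2.4085 and df = 298.
- Correlation computed directly from the data: 0.1382.
- Printed expression: 5.801/(5.801 + 298) = 0.0191, which is 0.1382².
- Square root of the printed expression: 0.1382.

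**Figure to reproduce.** None. The article states no numerical effect size.

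**Inputs for the size of the discrepancy.**
- Section 2.3.3: "A minimum sample size of 300 participants will be needed to detect an odds ratio of 1.5 in the primary outcome". A two-group t on 300 has df = 298.
- Section 2.2: "120 adolescents per city; 180 adolescents in the intervention and 180 in the control group". With all 360 analysed, df = 358.
- Section 2.3.3: "To account for the potential loss to follow-up of up to 50% participants regardless of gender". Half of 360 is 180, so df = 178.
- Section 6: "the level of significance will be set at *p* < 0.05". Two-sided testing is assumed, since sidedness is not stated. The critical t is then 1.968 at df = 298 and 1.967 at df = 358.
- The values of t are assumptions. The df count individuals, which section 2.1 names as the units of analysis, and ignore the few degrees of freedom that covariates would use.

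**Understatement factor.** Value with the root divided by value printed = r/r² = 1/r = sqrt[(t² + df)/t²].

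| t (assumed) | df | Printed: t²/(t² + df) | With root | Factor 1/r |
|---|---|---|---|---|
| 1.968 | 298 | 3.873/301.873 = 0.0128 | 0.113 | 8.8 |
| 3 | 298 | 9/307 = 0.0293 | 0.171 | 5.8 |
| 2 | 178 | 4/182 = 0.0220 | 0.148 | 6.7 |
| 1.967 | 358 | 3.869/361.869 = 0.0107 | 0.103 | 9.7 |
| 1 | 358 | 1/359 = 0.0028 | 0.053 | about 19 |
| 6 | 178 | 36/214 = 0.168 | 0.410 | 2.4 |

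Stated in terms of r itself, the factor is 10 at r = 0.1, 3.3 at r = 0.3 and 2 at r = 0.5. Over t from 1 to 6 and df from 178 to 358 it runs from about 19 down to about 2.4.

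**The case against.** **The root may have been lost in text conversion.** The text at hand is machine-read, and the outer square brackets do no work, because the inner parentheses already fix the order of operations. They could be what remains of a radical sign or a trailing exponent. This is possible but not shown: the superscript 2s and the brackets themselves survived. It justifies checking the typeset page first. If the root is there, the point falls.

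**Analysts may follow the cited source rather than the printed line.** That source is not available here, so this cannot be settled. The article nonetheless prints an explicit rule and defines its terms, and as printed the rule is wrong for its label.

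**The value is valid if read as variance explained.** True, and this is why relabelling is a sufficient remedy. It does not rescue the label r.

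**Stronger readings that the document does not support.**
- A reader might infer that every effect will look about nine times too small. That size arises only near the significance threshold with roughly 300 to 360 analysed. With no expected t or r in the article, no single factor can be claimed.
- A reader might blame the missing root for losing the direction of effect. The root is unsigned too. Direction has to come from the sign of t, and it is also carried by the planned regression of change scores on study group in section 6.
- A reader might infer that the trial's inference is compromised. No test, p-value, power figure or sample size uses this formula.

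Which model should supply the effect estimate is a separate matter, and nothing here rests on it.

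**Conclusion.** The point holds for the formula as it reads in section 6: the quantity labelled r is r². Taken as a correlation, it understates the effect by 1/r. At a just-significant result with 300 analysed, that means 0.013 where r is 0.113. The size of the discrepancy rests on assumed t values, on df counted over individuals, and on the typeset formula matching the text at hand. The consequence is confined to the effect-size metric, but that metric is an operative reporting rule covering all three primary outcomes, so it should be corrected before results are reported.

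**What to change.** First confirm the formula against the typeset article. If the root is absent, do one of the following:

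1. Write r = sqrt[t²/(t² + df)] and report it with the sign of t.
2. Keep the expression and relabel it r², or partial eta squared where t and df come from the ANCOVA, and give the direction of effect alongside.

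Whichever is chosen, the results should use the same name and scale throughout. The cost is one symbol or one label in section 6; no data, test or sample-size figure changes.
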